## 1. Introduction

A physically active lifestyle should begin at an early age and continue throughout the life cycle [1,2], with a synergistic relationship between physical activity and motor competence [3]. The development of fundamental motor skills (FMSs) is a favorable antecedent and significantly related to longer periods of moderate-to-vigorous physical activity (MVPA) in children (*p* < 0.05) [4]. FMSs denote the mastery of common basic motor skills with specific patterns; these can be classified as locomotor, object control, and stability skills, which favor the development of advanced and complex movements that allow participation in high-motor-engagement activities [4]. 

Thus, FMSs represent a key factor for healthy development in early childhood [5,6]. A systematic review conducted by Bolger et al. [7] showed that FMS competence increases with age during childhood, with locomotor skills being greater than object control. In addition, physical inactivity leads to impaired motor competence and correlates negatively with language development (β = −0.664; *p* = 0.004) in children aged 3 to 5 years [8]. Furthermore, Wang et al. [9] indicated that stability for the motor domain within each developmental area is high (motor competence) from 3 to 5 years of age, while unique prediction from one domain to the other is weak.

In this regard, a systematic review by Lin et al. [10] reported that FMS-focused physical activity interventions in children lead to improved postural control, motor competence and muscle strength compared to traditional physical education classes. In a meta-analysis conducted by Van Capelle et al. [11], FMS-focused interventions lasting 17 to 21 weeks with a frequency of 1 to 3 sessions of 17 to 35 min, led by teachers, significantly improved overall FMSs (SMD = 0.14; 95% CI = 0.06 to 0.21; *p* = 0.0003), object control (SMD = 0.47; 95% CI = 0.15 to 0.80; *p* = 0.004) and locomotor skills (SMD = 0.44; 95% CI = 0.16 to 0.73; *p* = 0.002) compared to children aged 3 to 5 years who were given no teacher-led FMS interventions. In another study, Han et al. [12] reported a moderate correlation between FMS scores in executive functions (r = 0.33; *p* < 0.001) and scores in locomotor skills, which were found to be significant predictors of inhibitory control (β = 0.21; *p* < 0.001), working memory (β = 0.18; *p* < 0.01) and cognitive flexibility (β = 0.24, *p* < 0.001) in children aged 3 to 5 years. 

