### 2.6. Intervention

The intervention will be implemented by early childhood educators, who will be trained about the objectives and contents of each session of CMSI that will be developed. Each session will take place in the classroom the preschoolers usually attend, which will depend on the admission policies of each educational community regarding the class levels (upper middle, transition level 1, and transition level 2). The intervention will last 12 weeks (36 sessions), distributed in 3 weekly sessions (Monday, Wednesday and Friday) of 40 min per session. CMSI is based on 2 previous studies [14,21], and a book related to CMSI [22]. Twelve unpublished motor stories will be distributed, one each week over 3 sessions, with the corresponding progressions for each session carried out. Thus, the children will be placed in a sequence of stories that begin with the presentation of a motivating character, who will accompany the children during the development of the whole story. The motor stories that will be developed each week are: (i) who I am; (ii) we go on an excursion; (iii) the school; (iv) the recess; (v) the weekend has arrived; (vi) visiting the park; (vii) my days in the field; (viii) my days at the beach; (ix) we go to the stadium; (x) we are going to know my environment; (xi) let’s go to the circus; (xii) tell me your adventures. The aim of the motor story translates into solving practical challenges while maintaining control, balance and coordination by combining various postures and movements such as throwing and receiving, moving on inclined planes and following rhythms, all in a variety of games and other activities [4,12,23].

The 40 min sessions will include three segments: (i) warm-up (5 min), which consists of joint mobility exercises and introduction to the motor story of the week; (ii) main part (25 min), which incorporates the narration of the motor story by the educator initially, as well as the participation of the children through their own corporeality with movements based mainly on FMSs (locomotion skills and object control), through two-way verbal interaction based on questions relating to the narration delivered by the educator or through direct verbal participation from each child; and (iii) cool down (10 min), where space is provided for the children to gradually return to calm, together with feedback on the content addressed during the session. Table 1 summarizes the materials and objectives of the weekly motor stories.

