### 2.7. Control Groups

The upper-middle-level control groups (n = 2 classes; n = 24 children), transition level 1 control groups (n = 2 classes; n = 24 children) and transition level 2 control groups (n = 2; n = 24 children) will participate in the assessments (initial and final) and will be asked to maintain their regular sessions at their educational establishments. At the end of the intervention period (according to the results obtained), the control group children, parents and/or legal guardians, managers and coordinators of each community will be contacted and provided with the material so that they can replicate the experience. In addition, the educators of these establishments (teachers and classroom assistants) will be trained in CMSI strategy.

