### 2.12. Intention-to-Treat Analysis

A two-factor repeated measures ANOVA will be used to determine the effects of the intervention on the outcomes (group × time). Post hoc tests will be performed with an alpha adjusted by Bonferroni to identify statistically significant differences. The effect sizes will be calculated utilizing Cohen’s d [36] within the group and between the groups, using the following equation: effect size = (post-mean − pre-mean)/standard deviation combined. The level of significance will be set at 5%. The intraclass correlation coefficient will be used to verify the measurement’s reliability, with a predetermined threshold of 0.80 being used to include the data in the analyses. Furthermore, logistic regression will be performed to identify the association of the physical activity level with FMSs, language development and morphological and sociodemographic variable factors. For all statistical analyses, the sociodemographic variables will be considered as moderators (covariates). 

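### The one equation given for Cohen's d is a within-arm pre-to-post change, so it cannot supply the between-group effect size it is also assigned to

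*Protocol article*

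**What the plan says.** All of the relevant text is in the protocol article.

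- **Effect size (section 2.12).** Cohen's d is to be calculated "within the group and between the groups, using the following equation". One equation follows: "effect size = (post-mean − pre-mean)/standard deviation combined". No second equation for the between-group case appears anywhere in the article.
- **Per-protocol analysis (section 2.13).** It repeats the intention-to-treat procedures, so it inherits the same equation.
- **Test of the intervention (section 2.12).** This is a separate step: "A two-factor repeated measures ANOVA will be used to determine the effects of the intervention on the outcomes (group × time".
- **Control data (section 2.7).** The control classes "will participate in the assessments (initial and final) and will be asked to maintain their regular sessions". Pre-test and post-test means will therefore exist for both arms.
- **Hypothesis (section 1).** It is comparative: the gains are expected relative to the control groups.
- **Change with age (section 1).** The introduction cites a review finding that "FMS competence increases with age during childhood".

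**The concern.** The numerator of the equation is one arm's post-test mean minus the same arm's pre-test mean. Nothing from the other arm enters. Taken literally it yields one d for each arm, or one for both arms together, and neither is a contrast between arms.

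The two assessments are separated by the whole intervention period (section 2.6: "The intervention will last 12 weeks (36 sessions), distributed in 3 weekly sessions"). Anything that moves both arms over that time enters the numerator in full: maturation, familiarity with the tests, or a seasonal trend in activity. If the result is then labelled a between-group effect size, the reader is given the sum of the shared change and the programme's effect as though it were the programme's effect alone. What is at stake is the meaning of the reported effect sizes, and whether they can be set beside controlled standardised differences such as those quoted in the introduction (0.44 for locomotor skills, 0.47 for object control).

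**Working it through.** The article reports no effect size computed with this equation, so there is no figure to reproduce. The check is algebraic, with a simulation to confirm it.

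**Inputs**
- The equation and its stated scope: section 2.12.
- 72 children per arm: section 2.3.
- δ, the true effect in SD units: 0 (null case), and 0.44 for illustration. The latter is the locomotor SMD in section 1. It comes from a meta-analysis of teacher-led motor-skill programmes and is not an estimate for this intervention.
- g, the change common to both arms in SD units: **assumed**, since the article gives none. Range shown: 0 to 0.5.

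**Algebra**, with a common SD:
- Experimental arm, printed equation: (post − pre)/SD = g + δ.
- Control arm, printed equation: g.
- Both arms together at 72 each, printed equation: [72(g + δ) + 72g]/144 = g + δ/2.
- Difference in change: (g + δ) − g = δ.

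Only the last line recovers δ. The experimental-arm value is off by exactly g.

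| Assumed g | Printed equation, δ = 0 | Printed equation, δ = 0.44 | Difference in change, δ = 0 | Difference in change, δ = 0.44 |
|---|---|---|---|---|
| 0 | 0.00 | 0.44 | 0.00 | 0.44 |
| 0.1 | 0.10 | 0.54 | 0.00 | 0.44 |
| 0.2 | 0.20 | 0.64 | 0.00 | 0.44 |
| 0.3 | 0.30 | 0.74 | 0.00 | 0.44 |
| 0.5 | 0.50 | 0.94 | 0.00 | 0.44 |

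**Simulation.** 4000 trials were run for each g, with 72 children per arm, δ = 0, an assumed pre-post correlation of 0.7 and no clustering by class. The printed equation used the SD combined over the experimental arm's two occasions. The control-adjusted d used the pre-test SD pooled over arms.

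| g | Mean d, printed equation | Mean control-adjusted d | Rejections at 5%, comparison of change scores |
|---|---|---|---|
| 0.2 | 0.20 | 0.00 | 5.1% |
| 0.3 | 0.31 | 0.00 | 5.0% |
| 0.5 | 0.51 | 0.00 | 5.1% |

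With two occasions, comparing change scores between arms is equivalent to the group × time test. It rejects at about its nominal level whatever g is, so shared change contaminates the effect size and not the interaction test. Because the simulation has no class clustering, it says nothing about how the ANOVA behaves under allocation by class, which is a separate matter.

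**The case against.** The strongest reply is that the article does not use this equation to decide whether the programme works. Section 2.12 gives that task to the group × time ANOVA, which removes any change common to both arms. **This stands.** A reader might infer from the equation that ordinary growth will be declared an intervention effect, or that the trial's main test is biased. The article supports neither.

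A second reply is that the literal equation would give the control arm its own d. In the null case with g = 0.3 the reader would see 0.30 beside 0.30 and draw the right conclusion. A within-arm d is a legitimate descriptive quantity, and the sentence may simply be loosely drafted. **This stands in part.** Showing both values would limit the harm, but the article does not say that the two are to be subtracted. It calls the equation's result a between-group effect size, which it is not. If a standard between-group d was intended, the sentence still needs correcting because it says something else. Nor is this a detail left to a fuller document: the article prints an equation and states its scope, and for half of that scope the equation is wrong.

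A third reply is that the size is unknown. **This stands.** The introduction says only that motor competence rises with age. It gives no gain over 12 weeks and says nothing of the kind about the language or activity outcomes. The ratio 0.74/0.44 = 1.68 might be read as a forecast of 68% inflation, but both of its inputs are illustrative. Age-normed scores would also remove part of the growth. Section 2.9.1 allows TGMD-2 standard scores and section 2.9.2 reports that the TELEPRE manual proposes T-scores, although the article does not fix either as the analysed score.

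**Conclusion.** The point holds as a defect in the definition of the effect size. The single equation in section 2.12 is a within-arm change and cannot yield the between-group d it is assigned to. The error carries into the per-protocol analysis through section 2.13. This much rests on the text alone.

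The consequence is limited to the reported effect sizes. Read as a between-group effect, the experimental-arm value is wrong by g, the change common to both arms. For an assumed g of 0 to 0.5 that is 0 to 0.5 SD: nothing if the control arm does not change, and less than the raw-score figure if age-normed scores are analysed. The identity assumes the same shared change and the same SD in both arms. The article supplies no value of g for any outcome, so no particular degree of inflation can be claimed. It is worth correcting before the results are reported, but it does not threaten the interaction test.

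**What to change.** In section 2.12, restrict the printed equation to descriptive within-arm change and say so. Then define the between-group effect size separately, in one of two ways:

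- d = [(post − pre) in experimental − (post − pre) in control] / pooled SD; or
- d = baseline-adjusted difference between arms at post-test / pooled SD.

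Name the SD; the pre-test SD pooled over both arms is a reasonable choice. Report the between-group d with a 95% CI that allows for allocation by class. Section 2.13 then takes on the corrected definition without further change.

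The cost is one sentence and one line of code. No new data are needed, since the control classes are assessed at both times. The downside for the authors is that between-group effect sizes will be smaller than the printed equation would give wherever the control arm also improves.

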## Abstract

This study protocol aims to analyze and compare the effects of combined movement and storytelling intervention (CMSI) on fundamental motor skills (locomotor skills and object control), language development (language comprehension, language expression, vocabulary and language description), and physical activity levels (light intensity, moderate-to-vigorous intensity and sedentary time) in children aged 3 to 6 years. The sample will consist of 144 children from 12 class groups, randomly assigned to 3 experimental groups (*n* = 72 children) and 3 control groups (*n* = 72 children), belonging to 4 class groups of upper-middle-level classes (2 experimental and 2 control; 3 to 4 years), 4 transition level 1 classes (2 experimental and 2 control; 4 to 5 years) and 4 transition level 2 classes (2 experimental and 2 control; 5 to 6 years). The experimental groups will perform CMSI for 3 sessions per week (40 min per session) over 12 weeks (using one motor story per week), while the control groups will not receive any treatment. The main outcome will provide information about fundamental motor skills, language development, and physical activity levels. Our hypothesis indicates that CMSI has the potential to generate significant increases in selected assessments. If this intervention proves to be beneficial, it could contribute to preschool and school curricula.

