Additionally, a systematic review by Jylänki et al. [13] reported that FMS interventions were effective in improving executive functions, language, arithmetic skills, cognitive skills, and memory in children aged 3 to 7 years; however, these studies presented a low methodological quality. In general, FMS proposals are based on locomotor skills, object control, and stability skills, with less common FMS strategies involving not only motor competence but also relating to motor stories that are used to stimulate the cognitive state of schoolchildren [14]. 

Combined movement and storytelling intervention (CMSI) is emerging as an FMS strategy that has shown significant improvements in motor, cognitive and linguistic skills in children [14,15]. In a study conducted by Eyre et al. [15], involving a non-randomized controlled trial with a 12-week CMSI, significant improvements (*p* ≤ 0.01) were reported in seven motor skills (run, jump, throw, catch, stationary dribble, roll and kick) in South Asian children aged 5 to 6 years. Similarly, Duncan, Cunningham and Eyre [14] conducted a randomized controlled trial over 6 weeks, using CMSI with preschool children in England, and reported significant improvements in motor (Δ 4.86; *p* = 0.001) and language (Δ 13.6; *p* = 0.001) skills compared to two active control groups. 

Taking into account the benefits of promoting FMSs at an early age and considering the dearth of scientific literature to date on novel strategies such as CMSI [14,15], it becomes relevant to analyze the possible changes/benefits of introducing CMSIs to preschool children. Therefore, this study protocol aims to analyze and compare the effects of CMSI on FMSs (locomotor skills and object control), language development (language comprehension, language expression, vocabulary and language description) and physical activity levels (light physical activity, LPA; MVPA; and sedentary behavior, SB)—in children aged 3 to 6 years. Based on previous studies [14,15], it is hypothesized that CMSI has the potential to generate significant increases in locomotor skills, object control, language comprehension, language expression, vocabulary, language description and MVPA level compared to control groups.

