### 2.3. Sample Size Calculation

Twelve children will be recruited from each class group (without gender distinction). The distribution of the class groups (12 class groups) will be in 3 experimental groups (6 class groups, n ± 72 children) and 3 control groups (6 class groups, n ± 72 children). The distribution by clusters or strata is justified by the fact that the use of individual randomization would imply a high probability of contaminating the control groups since it is unfeasible to prohibit children from interacting in school classrooms or recreational spaces (i.e., playgrounds, hallways, laboratories), which is where the study intervention will be carried out [18,19]. In addition, in the Maule region (one of the sixteen regions into which to Chile is divided; located in the center of the country and bordered to the north by the O’Higgins region, to the east by the provinces of Mendoza and Neuquén belonging to Argentina, to the south by the Ñuble region and to the west by the Pacific Ocean), there are 54 educational establishments that provide preschool education with an enrollment of approximately 1080 children. 

The sample size calculation indicates that the ideal number of participants per group is 10. As agreed in a previous study by Eyre et al. [15], we will use a mean difference of 3.22 total score of locomotor skill domains for this calculation as the minimum difference necessary for substantial clinical relevance, with a standard deviation of 0.70 points, considering an alpha level of 0.05 with a power of 80% and an expected loss of 15%. The GPower program (version 3.1.9.6, Franz Faul, Universiät Kiel, Kiel, Germany) will be used to calculate the statistical power. 

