### 2.9. Primary Outcomes

#### 2.9.1. Fundamental Motor Skills (FMSs)

These will be assessed by means of the test of gross motor development-second edition (TGMD-2) [24]. This battery measures 12 FMSs in two different domains (locomotor skills and object control). The locomotor skills domain contains 6 assessments: (i) running, (ii) galloping, (iii) hopping on one foot, (iv) long jumping, (v) horizontal jumping and (vi) lateral sliding. The object control domain also includes 6 assessments: (i) batting a stationary ball, (ii) stationary dribbling, (iii) catching a ball, (iv) kicking a ball, (v) throwing a ball and (vi) rolling a ball. Estimated administration time is ≤10 min per child. The 6 locomotion skills and 6 object control skills incorporate 24 criteria, allowing a total score from 0 to 48 points. The domain scores can be transformed into a standard score (median = 10.0 and standard deviation = 3.0) and subsequently into a gross motor quotient (median = 100.0 and standard deviation = 15.0). This information can be found in percentiles that allow the child to be placed in normative values with respect to a reference population. The original TGMD-2 reports high test–retest and inter-rater reliability (all r values > 0.85), as well as good internal consistency that varies between 0.85 and 0.88 for each ability [24]. In addition, its content, construct and concurrent validity have been demonstrated in children aged ≥ 3 years in countries such as Chile [25,26], Brazil [27] and Korea [28]. 

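### Nine unranked primary variables are tested at 5% and the stated Bonferroni step covers only post hoc tests, so nothing stated controls false positives across the primaries

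*Protocol article*

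**What the plan says.** Protocol article, under the heading "2.9. Primary Outcomes": section 2.9.1 covers motor skills in two domains (locomotor, object control), 2.9.2 covers language in four domains (comprehension, expression, vocabulary, description), and 2.9.3 covers accelerometer-measured light activity (LPA), moderate-to-vigorous activity (MVPA) and sedentary behaviour (SB). That makes nine variables, and none is placed ahead of the others. The abstract uses the singular but names all three constructs: "The main outcome will provide information about fundamental motor skills, language development, and physical activity levels".

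The Introduction predicts "significant increases in locomotor skills, object control, language comprehension, language expression, vocabulary, language description and MVPA level compared to control groups". That is seven of the nine; LPA and SB are primary but carry no predicted direction.

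Section 2.12 uses a two-factor repeated measures ANOVA (group by time) for the outcomes. On error control it says "Post hoc tests will be performed with an alpha adjusted by Bonferroni to identify statistically significant differences" and "The level of significance will be set at 5" per cent.

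Section 2.3 sizes the trial on one variable: "we will use a mean difference of 3.22 total score of locomotor skill domains", "with a standard deviation of 0.70 points, considering an alpha level of 0.05 with a power of 80% and an expected loss of 15" per cent.

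**The concern.** A Bonferroni correction of post hoc tests ordinarily limits error among the pairwise comparisons that follow one ANOVA. It does nothing for the error that builds up when nine separate group-by-time tests are each read at 5%. The article states no order of testing, no split of alpha, and no requirement that all primaries succeed. Under the rules as written, any one significant primary could be reported as the trial's positive result. The article says a beneficial result could feed into preschool and school curricula, so it matters how easily one of nine variables can be significant by chance.

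**Working it through.** **The plan's own figures.** The article gives no error rate across outcomes, so there is none to reproduce. Its one related figure is the sample size: "The sample size calculation indicates that the ideal number of participants per group is 10". From the stated inputs, d = 3.22/0.70 = 4.6. An exact two-sided t calculation at 5% and 80% power then needs 3 per group, or 4 after 15% loss. The stated 10 is not reproduced. That is a separate matter, and the results below do not depend on it.

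**Inputs**
- Number of primary variables: 2 + 4 + 3 = 9 (sections 2.9.1 to 2.9.3).
- Variables in the directional hypothesis: 7 (Introduction).
- Level per test: 0.05 (section 2.12). A group-by-time F test is non-directional. With two arms and two time points, half of the 5%, or 0.025, falls in the direction favouring CMSI.
- Correlation between test statistics: not given. I assume 0 to 0.8, with statistics oriented so that positive values favour CMSI.
- CMSI has no effect on any variable, and each test truly has 5% error.

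**Independent tests.** Any false significant difference: 1 − 0.95^m. Any false difference favouring CMSI: 1 − 0.975^m.

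| Tests (m) | Either direction | Favouring CMSI |
|---|---|---|
| 9 (all primaries) | 1 − 0.95^9 = 37.0% | 1 − 0.975^9 = 20.4% |
| 7 (hypothesised) | 1 − 0.95^7 = 30.2% | 1 − 0.975^7 = 16.2% |
| 3 (one score per construct) | 1 − 0.95^3 = 14.3% | 1 − 0.975^3 = 7.3% |

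**Correlated tests.** Nine multivariate normal statistics with a common correlation, 300,000 simulated sets per setting:

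| Correlation | Either direction | Favouring CMSI |
|---|---|---|
| 0.2 | 34.9% | 18.0% |
| 0.3 | 32.6% | 16.5% |
| 0.5 | 26.9% | 13.5% |
| 0.8 | 16.6% | 8.3% |

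With correlations of 0.5 to 0.7 within a construct and 0.1 to 0.3 between constructs, the results are about 27% to 33% and 14% to 17%.

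**After adjustment.** Bonferroni over nine gives 0.05/9 = 0.0056 per test. The familywise error is then 1 − (1 − 0.0056)^9 = 4.9% under independence, and lower with positive correlation (2.4% at 0.8).

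**The case against.** **Nine tests is an inference.** Section 2.12 speaks only of the outcomes and never says nine ANOVAs. Section 2.9.1 also mentions a total score and a gross motor quotient. This stands as a caveat on size. But the aim itself enumerates the nine variables, and three tests would still give 14% in either direction and 7% favouring CMSI.

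**The Bonferroni family is not defined.** The text does not say in so many words that the adjustment works within one ANOVA. That is true, but it is attached to post hoc tests, and nothing extends it to the main group-by-time tests.

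**A condensed article may leave multiplicity to a fuller plan.** A bare omission would indeed be no finding. Here, however, the article fixes the primaries, the significance level and where the adjustment applies. Followed as written, those rules leave error across the primaries uncontrolled.

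**The hypothesis might require all seven increases.** It lists seven expected increases, but nowhere makes joint significance the condition for success.

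**Independence is the least plausible case.** This is fair. The motor and language domains are parts of single instruments, and the three activity measures share the same wear time. The independent figures therefore belong at the upper end of a range.

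**Conclusion.** The point holds. Nine unranked primaries are read at 5%, and the only stated adjustment is for post hoc tests. If the nine are tested separately, the chance of at least one false significant difference is 37% under independence and about 17% to 35% at assumed correlations of 0.8 to 0.2. In favour of CMSI it is about 20%, and 8% to 18% over the same correlations, against 2.5% for a single test. These figures assume no true effect on any variable and a two-arm comparison. The directional figure for nine also assigns a favourable direction to LPA and SB, which the hypothesis does not; for the seven hypothesised variables it is 16%.

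A reader might infer a one-in-three chance of falsely concluding that CMSI works. The documents do not support that: about one in three counts differences in either direction at low correlation, including those favouring control. A reader might also add that randomising whole classes inflates these figures further. That is a separate question about the validity of each test, and it cannot be sized here because the article gives no intraclass correlation for classes.

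**What to change.** In section 2.12, apply Holm (or Bonferroni at 0.05/9 = 0.0056) to the group-by-time tests across the nine primary variables, and state that an effect will be claimed only for variables significant after adjustment. This keeps the aim, which treats motor skills, language and physical activity equally. Bonferroni for post hoc comparisons can stay as a separate step.

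If the sponsor prefers a single primary, the locomotor score used in section 2.3 is an option: test it at 5%, and test the other eight by Holm only if it is significant. The gate matters. An ungated Holm family at 5% beside the primary would allow nearly 10% overall (1 − 0.95 × 0.95 = 9.75% if independent). This option also demotes language and activity, which changes the study's question.

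The change costs wording only, but it makes thresholds stricter and lowers power per outcome. As a guide under a normal approximation, a test with exactly 80% power at 5% has an expected z of 1.96 + 0.84 = 2.80. At 0.0056 the critical value is 2.77, so power falls to about 51%. Holm does no worse than this and does better when several outcomes respond. The article gives planning values for the locomotor score only, so the loss for the other eight cannot be worked out from it.

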### 2.8. Outcomes and Procedures

The first meeting will be to obtain the agreement of the educational establishments and educators, to obtain the necessary signatures of informed consent and to explain the scope and aim of the study; also, the children will be randomly assigned to the intervention groups. During the following 2 weeks, the first assessments (pre-tests) will be carried out, before the 12-week CMSI is implemented; finally, the second assessments (post-tests) will be administered. One of the researchers will supervise all of the assessments and CMSI, and there will be a predefined order that will be followed by expert personnel in the assessments: (i) FMSs (physical education teacher specializing in early childhood care); (ii) language development (kindergarten teacher); (iii) physical activity level (physical education teacher); (iv) morphological variables (anthropometrist); and (v) sociodemographic variables (kindergarten teacher and physical education teacher). Figure 2 shows a summary of the assessments and sessions that are usually part of CMSI.

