### 2.13. Analysis by Protocol

For this analysis, only children who have completed more than 85% of the sessions will be included. The same procedures will be performed as those indicated for the intention-to-treat analysis.

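### The intention-to-treat section makes inclusion of data depend on an ICC of 0.80, so a primary domain, or one assessor's or class's data, could be removed after collection

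*Protocol article*

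**What the plan says.** Section 2.12 of the protocol article is headed as the intention-to-treat analysis. It plans the main comparison ("A two-factor repeated measures ANOVA will be used to determine the effects of the intervention on the outcomes (group × time" interaction) and, in the same paragraph, a reliability check: "The intraclass correlation coefficient will be used to verify the measurement’s reliability". To that check it attaches a rule for inclusion: "with a predetermined threshold of 0.80 being used to include the data in the analyses".

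The section does not say what counts as the data (an outcome domain, a test item, an assessor, a class), which form of ICC is used, at which visit or on how many children it is estimated, or whether the estimate or a confidence limit is held against 0.80.

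Section 2.13 adds no exemption for the per-protocol analysis: "The same procedures will be performed as those indicated for the intention-to-treat analysis".

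On timing, Section 2.8 describes a first meeting at which consent is obtained and "also, the children will be randomly assigned to the intervention groups". The baseline measurements come after that: "During the following 2 weeks, the first assessments (pre-tests) will be carried out".

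On expected reliability, Section 2.9.1 cites for the original motor test (TGMD-2) "high test–retest and inter-rater reliability (all r values > 0.85". Section 2.9.2 gives the language test (TELEPRE) an internal consistency of 0.87 to 0.93 and no ICC.

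**The concern.** An intention-to-treat analysis should keep all randomised children in their assigned arms, and the set of primary outcomes should be fixed before results are known. An inclusion rule that turns on a statistic estimated from the trial's own measurements can disturb both.

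An ICC describes a set of measurements, so the clause would naturally act on a set. Two cases differ in what they cost:

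- **A whole domain fails.** For example, object control is dropped for everybody. The remaining outcomes keep all their children, but which primary outcomes are reported now depends on the data.
- **The data of one assessor or class fail.** Randomised children then lose their outcome data, and the analysed set is no longer the intention-to-treat set. Classes are the randomised units (six per arm), so losing one is a large loss to that arm.

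Because the unit, visit and form of ICC are open, these choices could also be made once the data are in hand.

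This is separate from the 85% attendance criterion in Section 2.5. Correcting that criterion would leave this clause in force.

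**Working it through.** **Step 1. Can the rule act after assignment?** The 0.80 is a set threshold, so there is no derived figure to reproduce. Read together, Section 2.8 puts assignment at the first meeting and the pre-tests in the two weeks after it; Section 2.12 puts the threshold inside the intention-to-treat analysis; Section 2.13 repeats it per protocol. Any ICC computed from trial measurements is therefore known only after assignment, and one from the post-tests only after the intervention. No section places the check in a pilot or in assessor training.

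**Step 2. How often would an adequate measure fail by chance?**

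Inputs from the article: threshold 0.80 (Section 2.12); 144 children (Section 2.5); r above 0.85 for the motor test (Section 2.9.1), used only as a guide because it is not an ICC from this trial.

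Assumptions: one-way ICC; two measurements per child (k = 2); the point estimate is compared with 0.80; n children in the reliability check (30, 50 or all 144); true ICC ρ of 0.82 to 0.90.

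Formulas, with F the ratio of between-child to within-child mean squares:

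- Observed ICC = (F − 1)/(F + 1) for k = 2. Setting this to 0.80 gives F = 1.80/0.20 = 9.
- F is distributed as (1 + ρ)/(1 − ρ) times a central F variable with n − 1 and n degrees of freedom.
- So P(observed ICC < 0.80) = P(F(n − 1, n) < 9(1 − ρ)/(1 + ρ)).

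For ρ = 0.85 the cut-off is 9 × 0.15/1.85 = 0.730. For ρ = 0.88 it is 9 × 0.12/1.88 = 0.574.

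| True ICC | n = 30 | n = 50 | n = 144 |
|---|---|---|---|
| 0.82 | 38% | 34% | 24% |
| 0.85 | 20% | 14% | 3% |
| 0.88 | 7% | 3% | under 0.1% |
| 0.90 | 2% | 0.5% | about 0% |

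**Step 3. At least one of the two motor domains.** If the locomotor and object control domains are independent, the chance is 1 − (1 − p)². With ρ = 0.85:

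- n = 30: 1 − (1 − 0.199)² = 36%
- n = 50: 1 − (1 − 0.136)² = 25%
- n = 144: 1 − (1 − 0.030)² = 6%

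The same children are tested in both domains, and positive dependence would lower these figures. I do not extend them to the four language domains, because the article gives no ICC for that test and internal consistency is a different quantity.

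**Step 4. The opposite error.** A measure with a true ICC of 0.75 would still pass in about 25% of checks on 30 children and 7% on 144. In a small check the rule is a weak filter in both directions.

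**The case against.** The strongest reply is that the authors meant a qualification check on assessors. The wording about verifying reliability fits that, the threshold is fixed in advance and does not look at the treatment effect, and a condensed article may leave the operational detail to a fuller document. This stands in part: use of trial data and of a point estimate is inferred and not stated. But what is printed is an inclusion rule inside the intention-to-treat section, and nothing there limits it to a step before the trial.

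Second, on the pooled reading a failing domain disappears from both arms alike, and every other outcome keeps all its children. That is right. The harm in that case is a data-dependent outcome set, not bias between arms.

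Third, a reliability safeguard has a purpose. Random error widens the confidence interval, but systematic differences between assessors can bias the comparison if assessors are unevenly spread over classes. This also stands, and is a reason to move the threshold and not to abandon reliability checking.

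Fourth, the percentages depend on assumptions, and 0.85 is the excluded lower bound of the cited r values. With a true ICC of 0.90 and all 144 children measured twice, chance failure is negligible.

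A reader might go further and infer that individual children will be dropped, or that exclusion will differ by arm. The documents support neither. An ICC does not belong to one child, and no section computes it by arm; Section 2.4 has external professionals take the measurements.

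**Conclusion.** The point holds in a limited form. As printed, the clause lets an observed reliability estimate decide which collected primary-outcome data are analysed, in both planned analyses. If the ICC is taken from trial measurements, loss of a domain makes the primary outcome set data-dependent, and loss by assessor or class also breaks the intention-to-treat set. That conclusion rests on the text and on none of the percentages.

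The size is uncertain. It matters if reliability is checked on a few dozen children or the true ICC lies near 0.80, and matters little if all children are measured twice and the true ICC is about 0.90. The change should be made. It affects no sample-size, power or alpha figure.

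**What to change.** Replace the threshold clause in Section 2.12 with wording such as: *The ICC with its 95% CI will be reported for each measure to describe reliability; it will not determine which data are analysed, and all available data from all randomised children will be included in the intention-to-treat analysis.*

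If a 0.80 threshold is wanted, apply it to assessor certification before baseline testing, or to a sensitivity analysis labelled as such. Section 2.13 then inherits the corrected wording.

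The cost is one sentence, plus a certification exercise if that option is taken. The downside is that some noisier data stay in the primary analysis: random error there shows as wider intervals, while systematic assessor differences have to be handled by certification.
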